
### Metabolomics of follicular fluid

For metabolomics analysis, the metabolites will be extracted using a solvent mixture containing isopropanol: acetonitrile: water (2:1:1). Four volumes of the cold solvent will be added to one volume of sample. The samples will be homogenized by mixing and gentle shaking. The proteins will be precipitated by incubating the mixture at −20 °C for 1 h. After centrifugation (9,000 g/15 min/4 °C), the organic layer will be carefully removed and transferred on to a new tube. The tube will be subjected to flash evaporation using nitrogen and dried completely. A solution containing 5% acetonitrile with 0.1% formic acid will be used for redissolving the dried organic phase and further subjected to LC–MS/MS analysis. The analyses will be performed on a C18 column (Agilent Zorbax; 150 × 2.1mm, 2.7 μM) through a uHPLC system. LC–MS/MS analysis will be performed using a Q-TOF mass spectrometer (Agilent Technologies) equipped with the Dual AJS source. Infusion of reference mass ions (118.0862, 322.0481, 922.0097, 2121.9331) will ensure high mass accuracy over a wider mass range. 100% water with 0.1% formic acid will be used as mobile phase A and 100% acetonitrile with 0.1% formic acid will be used as mobile phase B. A liner gradient of 5–95% B for 45 min and a flow rate of 200 μL/min will be set, and the peaks will be monitored at 254 nm using a diode array detector. MS data will be acquired in both positive and negative ionization mode with a fixed collision energy. The other parameters that will be used for the MS data acquisition includes; nebulizer pressure; 15.0 psi, dry gas flow: 10 L/min, dry gas temperature; 350 °c, scan range; 50–2000 m/z, no of precursors; 5.

The raw data will be processed using Agilent MassHunter qualitative analysis software (Version 7.0) enabling the molecular feature extraction module. The data obtained will be aligned using their respective retention time and m/z values. The molecular feature extraction workflow enables in the identification of the respective compounds through aligning the respective retention time and m/z values. Subsequently, the elemental composition analysis (of monoisotopic m/z or the average isotopic m/z values) will be performed using the formula finder tool in the MassHunter software. The data will be further filtered to make sure like only validated and high-quality data will be further taken for the analysis. The intensity threshold will be set for minimizing the influence of signal to noise ratio for the accurate identification. The metabolites present will be identified incorporating all the stringent conditions including retention time, monoisotopic masses, ion intensity. Followed by this, the information of all the compounds will be identified and searched using the Agilent MassHunter PCDL (Personal Compound Database and Library). For metabolome analysis, the collected data, after filtering and extraction process will be searched using PubChem (National Center for Biotechnology Information), ChemSpider, Agilent Metabolomics Lab, METLIN (Scripps Center for Mass Spectrometry), KEGG (Kyoto Encyclopedia of Genes and Genomes) and HMDB (Human Metabolome database). The structure and identity will be viewed through the ‘compound find’ tab in the MassHunter qualitative analysis software. Finally, heatmaps, principal component analysis and multivariate statistical analysis will be performed using ‘R’ and Bioconductor package. All the metabolite data information collected will be also normalized using MetaboAnalyst 6.0. Principal component analysis will be used to evaluate the quality, identify outliers, and display global patterns in the metabolomic data of follicular fluid. Through MetaboAnalyst, supervised modelling will be carried out using partial least squares–discriminant analysis (PLS-DA) to find metabolite signatures that differentiate DOR participants from controls. A nested cross-validation will be performed using an outer five-fold loop and inner three-fold loop for estimating unbiased performance and for feature selection, respectively, as indicated in the MetaboAnalyst pipeline. To cross validate the model performance, root mean squared error (RMSE), *R*^2^, and permutation testing will be done. Further, the differentially regulated metabolites (fold change ≥1.5) will be evaluated using Benjamini–Hochberg (5% FDR) correction, and features that are chosen several times will be given higher priority as strong candidates. These metabolites will be finally correlated with the obtained AMH and AFC data. Figure 2 illustrates the overall multi-omics workflow adopted in the study.

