### Sample size

The sample size calculation was done using G*Power (version 3.1.9.7) (23) based on a previous study data. The initial sample size calculated to detect an effect size of 0.58 for a two-sided significance level of 0.05 and 80% power was 26. To account for feasibility considerations and an anticipated 20% dropout, the final sample size was set at 30 participants. Since the present study is planned as an exploratory study, this sample size is not meant to give confirmatory inference, rather this study is planned to provide preliminary data regarding the role of an Ayurvedic treatment protocol in women with reduced ovarian reserve.

Follicular fluid will be collected from 10 participants who undergo Ayurveda treatment and 10 control participants who is receiving a contemporaneous IVF stimulation protocol for performing multi-omics analysis (matched by age and baseline AMH/AFC). No formal sample size calculation was performed for the multi-omics analysis, as it is hypothesis-generating and intended for exploratory purposes. Because the 10 controls included are for exploratory multi-omics analysis only, no clinical inference will be drawn between treatment and control groups.

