Follicular fluid from 10 control participants and 10 Ayurvedic-treated participants chosen from the 30-participants treatment arm and matched according to age and baseline AMH/AFC will be obtained for the secondary, exploratory multi-omics analysis. All the laboratory experiments will be performed in triplicates (of each biological samples) and statistical analysis will be done using GraphPad Prism software. The statistical analysis of collected proteome data will be performed using Proteome Scaffold software (version 4). Peptide identifications will be accepted if they can be established at greater than 95.0% probability. The Scaffold Local FDR algorithm and peptide prophet algorithm with scaffold delta-mass correction will assign peptide probabilities. Protein identifications will be accepted if they can be established at greater than 99.0% probability and contain at least two peptides representing the protein family. The protein prophet algorithm will assign protein probabilities (34, 35). For metabolomics analysis, after data generation, the heatmaps, principal component analysis, and multivariate statistical analysis will be performed using R (Version 4.5.1) and MetaboAnalyst 6.0. To evaluate the differences between the treatment and control groups in transcriptomics, proteomics, and metabolomics, *t*-tests (for normally distributed data) or Mann–Whitney U tests (for non-normal data) will be used for each gene, protein, or metabolite. To account for multiple comparisons, the Benjamini–Hochberg FDR correction will be used; an FDR of less than 0.05 will be considered significant. As described under each section, specific assays will be used to further validate the most important genes and proteins. No formal sample size calculation was performed for the exploratory multi-omics analysis, as it is hypothesis-generating, and the 10 treatment samples were selected based on matching and feasibility.

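### The metabolomics section, read literally, applies the 5% FDR correction only to metabolites already selected on observed fold change; Statistical methods corrects over all, and the two must be reconciled

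*Protocol article*

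**What the plan says.** Two parts of the protocol article set the rule for differential metabolites.

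- **Metabolomics of follicular fluid:** "the differentially regulated metabolites (fold change ≥1.5) will be evaluated using Benjamini–Hochberg (5% FDR) correction". The same section then carries these metabolites into correlations with AMH and AFC.
- **Statistical methods:** for the treatment-control comparison in all three omics layers, a t-test or Mann–Whitney test "will be used for each gene, protein, or metabolite". BH then handles multiplicity, and "an FDR of less than 0.05 will be considered significant". No fold-change step appears.

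The groups are small: "Follicular fluid from 10 control participants and 10 Ayurvedic-treated participants chosen from the 30-participants treatment arm". The Sample size section gives the status of this work: "No formal sample size calculation was performed for the multi-omics analysis, as it is hypothesis-generating and intended for exploratory purposes".

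For genes, the transcriptomics section describes BH first and uses the 1.5-fold threshold to pick genes for qRT-PCR. For proteins, the proteomics section uses the same threshold to pick candidates for ELISA and Western blotting.

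**The concern.** BH controls the FDR at its nominal level when the p-values of unaffected features are uniform within the family it is given. A filter that ignores group membership, such as an intensity or quality filter, preserves this. A filter on the observed group difference does not, because fold change is the numerator of the t-statistic in another form. Unaffected metabolites that survive are those that happened to show a large difference, so their p-values are already shifted towards zero. BH is then also told that the family is only as long as the list of survivors.

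At stake is the meaning of the 5% label on the metabolite list. Identifying key metabolites is a secondary objective. The list feeds the AMH and AFC correlations and, under Integration of multiomics data, the KEGG enrichment and pathway mapping. A hypothesis-generating study is only as useful as its list of candidates.

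**Working it through.** **Inputs from the article:** 10 v 10; fold change of at least 1.5; BH at 5%; t-test or Mann–Whitney.

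**Assumptions, because the article gives no figures:** 1000 metabolites, independent, roughly normal on the log2 scale with a common SD; fold change taken as the difference in mean log2 level.

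**Step 1: the stated 5%.** With BH over all metabolites, as in Statistical methods, the simulated chance of any false hit under no effect is about 5%. A separate grid (500 metabolites; 0, 5 or 20% truly changed) gave a realised FDR of 4.0–5.2%. The article's figure is therefore reproduced under that rule.

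**Step 2: how many null metabolites pass the filter.** The threshold is log2(1.5) = 0.585. The standard error of the difference is SE = SD × √(1/10 + 1/10) = 0.447 × SD. The pass share is f = 2 × [1 − Φ(0.585/SE)].

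| log2 SD | 0.585/SE | f | expected null survivors of 1000 |
|---|---|---|---|
| 0.3 | 4.36 | 0.000013 | 0.013 |
| 0.4 | 3.27 | 0.0011 | 1.1 |
| 0.5 | 2.62 | 0.0089 | 8.9 |
| 0.7 | 1.87 | 0.062 | 62 |
| 1.0 | 1.31 | 0.191 | 191 |
| 1.2 | 1.09 | 0.276 | 276 |

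**Step 3: what BH on the survivors does.** Two limits explain the pattern.

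- *Small SD.* Almost every survivor is already significant (at SD 0.5, 98% of null survivors have p < 0.05). The chance of a false hit is then close to the chance that anything survives, 1 − (1 − f)^1000. This is 1.3% at SD 0.3, 66% at 0.4 and nearly 100% at 0.5.
- *Large SD.* The metabolites with the smallest p-values nearly all pass, but the family shrinks from 1000 to 1000 × f. BH at 5% on the survivors then acts like BH over all at 0.05/f. This is 0.05/0.062 = 81% at SD 0.7, 0.05/0.191 = 26% at 1.0 and 0.05/0.276 = 18% at 1.2.

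**Step 4: simulation (t-test).** The results agree with these approximations.

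| log2 SD | any false hit, no effect: filter then BH | realised FDR, 10% truly changed 2-fold: filter then BH |
|---|---|---|
| 0.3 | about 2% | about 0% |
| 0.4 | 65% | 1% |
| 0.5 | 100% (about 9 false hits) | 8% |
| 0.7 | 77% | 26% |
| 1.0 | 28% | 17% |
| 1.2 | 20% | not run |

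BH over all gives about 5% in both settings.

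**Step 5: sensitivity.** In the 500-metabolite grid at a natural-log SD of 0.5 (0.5/0.693 = 0.72 in log2) with 5% truly changed, the realised FDR under filter-then-BH was 38%. It was 37–39% with 100 or 2000 metabolites. With the Mann–Whitney test it was 34–36% at that SD but only 3–4% at a natural-log SD of 0.7. The size of the excess therefore depends on the test as well as on the SD.

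**Step 6: the reversed order.** BH over all, with the 1.5-fold rule applied afterwards, gave a realised FDR of 0.8–5.2% across the 500-metabolite grid.

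**The case against.** The strongest reply is that the order is inferred. The metabolomics sentence has no word such as first or then and does not define the BH family. Its parenthesis might merely describe what counts as differentially regulated. Statistical methods is the natural home of the rule, and under it 5% holds. This stands in part: the article does not settle the order. But the plain grammar of the metabolomics sentence makes the fold-change set the thing that is corrected, and an analyst following that section would use the order that does not guarantee the label.

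A reader might be tempted by three stronger readings, none of which the article supports.

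- *That the 5% FDR is not delivered.* Statistical methods delivers it. Even under the literal order, the realised rate is about 5% or less when variability is small.
- *That a study with no effect will usually report false metabolites.* This is true only for a band of assumed SDs. It fails at log2 SD 0.3 and at 1.0 and above, and the article gives neither SDs nor a metabolite count.
- *That genes and proteins share the fault.* Their sections use the 1.5-fold threshold to choose candidates for laboratory validation, not to define a BH family.

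It is also fair to say that the work is labelled exploratory and that the metabolomics section adds nested cross-validation, permutation testing and priority for repeatedly selected features. These limit the harm but do not restore the FDR. An exploratory label does not excuse a stated error rate that may not hold.

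**Conclusion.** The point holds as a conflict between two sections. Read literally, the metabolomics section corrects only a list chosen on the outcome of the same comparison; Statistical methods corrects over every metabolite. Under the first order 5% FDR is not guaranteed, and the true rate can run from near zero to several times nominal. This range rests on the assumed 1000 independent metabolites, a common SD and the t-test. The direction of the problem does not: selecting on the observed group difference makes null p-values non-uniform whatever the SD.

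The consequence is confined to a secondary, exploratory list and what follows from it (pathway mapping and the AMH and AFC correlations). It is worth correcting because the remedy is trivial and changes which metabolites are reported.

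**What to change.** In Metabolomics of follicular fluid, replace the sentence so that it states three things in order:

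1. p-values are computed for every metabolite that passes quality filters applied without regard to group;
2. BH at 5% is applied across all of these, as in Statistical methods;
3. a fold change of at least 1.5 is used only afterwards, as a reporting threshold.

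This costs one sentence and no new data. The downside is that fewer metabolites may be called significant. The transcriptomics and proteomics sections need no change on this ground.

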
**Figure 2 fig2:**
[figure not shown]
The overall workflow for **(a)** proteomics **(b)** metabolomics and **(c)** transcriptomics analysis. (Created in BioRender. [name] (2025) https://BioRender.com/gux0gyw).

### Integration of multiomics data

The transcriptomics, proteomics and metabolomics data will be processed separately. The differentially expressed genes compiled after transcriptomics analysis will be studied in detail through ingenuity pathway analysis to study the upstream regulators, signalling pathways involved. Similarly, KEGG analysis will be used to determine the biological pathways that are enriched with differentially expressed proteins and metabolites. Finally, Multi-Omics Factor Analysis (MOFA) will be performed using the MOFA2 package in the Bioconductor software package (release 3.21). For this, the multiomics data obtained will be trained and analyzed to correlate with the AMH and AFC changes at 1% FDR with BH correction. Significant genes, proteins, and metabolites will be mapped onto biological pathways or networks, and correlations with clinical outcomes (AMH/AFC changes) will be explored to highlight mechanistically relevant associations.

## Data collection

On recruitment, participant consent will be obtained and documented in an Informed consent form (ICF) prepared in both Malayalam and English language. The basic demographic data, detailed medical history, baseline assessment details and all other relevant data will be collected and documented in an analog case report form (CRF). These will be done by the project research scientist at Amrita School of Ayurveda.

Clinical data collection: The baseline and post intervention clinical data for analysis will be collected through a blood test and ultrasound scan by experts at Amrita Fertility Centre and laboratory associated with the centre. To ensure consistency, reduces inter observer variability and improves reliability the same radiologist will perform the sonography and laboratory samples will be analysed at the same lab. To ensure quality assurance and reproducibility, standard operating procedures (SOPs) will be followed at every level of data collection and handling. Laboratory technician evaluating the biological samples and radiologist, will continue to be blind to the treatment schedules and clinical results to further enhance scientific rigour.

Follicular fluid collection: The follicular fluid will be collected from 10 participants who visit Amrita Fertility Centre after Ayurvedic treatment. Follicular fluid from 10 participants who did not avail of Ayurvedic treatment protocols undergoing IVF treatment will also be taken as control. During oocyte retrieval procedure, the follicular fluid will be aspirated from multiple follicles by the principal investigator, a Professor of Reproductive Medicine at Amrita Fertility Centre. The follicular fluid collected, after removing the cell debris through centrifugation (700 g for 10 min), will be immediately transferred to liquid nitrogen contained in the cryocan and transported to Amrita School of Biotechnology, by the project research scientist who is trained on handling and pre-processing the follicular fluid samples for performing multi-omics analysis. These samples will be transported to Amrita School of Biotechnology using a cryocan (with liquid nitrogen). Further, the follicular fluid samples will be divided into multiple aliquots in 5 mL Eppendorf tubes to avoid repeated freeze–thaw cycles and these aliquots will be stored in −80 °C till further analysis.

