### Multiomics analysis methodology

#### Transcriptomics of granulosa cells

Follicular fluid collected will be aspirated and pooled during the retrieval of oocytes. Granulosa cells will be isolated from the follicular fluid by centrifugation at 700 g for 10 min using percoll-mediated density gradient centrifugation. The layer with the cells will be carefully removed using a pipette and transferred to a fresh tube with the cell storage medium (10% FBS with DMSO). Total RNA will be extracted from the cells using TRIzol reagent. RNA purity and concentration will be assessed using Nanodrop2000 spectrophotometer (Thermo Fischer Scientific) with samples showing A260/280 between 2.0 to 1.8 considered acceptable and outsourced to MedGenome, Bangalore, India for library preparation and RNA sequencing. The quality of the raw reads will be checked using FastQC and MultiQC. Adapter trimming and low quality read removal will be performed using Trimmomatic v0.39 and the resulting clean reads will be aligned to the human reference genome with STAR (v2.7.10a). Gene counts will be obtained with feature Counts (v2.0.3) and analysed using DESeq21.34.0 in R software. Differential gene expression profiles will be analyzed comparing the control and treatment samples. False positives will be analyzed through Benjamini–Hochberg correction method. The adjusted *p*-value (FDR) less than 0.05 will be considered statistically significant. Following normalization, the gene enrichment analysis will be performed. The top upregulated and downregulated genes (≥1.5-fold) will be further validated using qRT-PCR using specific primers for the selected genes. The relative quantification of genes will be performed through comparative CT analysis.

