#### Proteomics of follicular fluid

The follicular fluid collected will be subjected to percoll-mediated density gradient centrifugation. The samples will be centrifuged at 700 g for 10 min and the supernatant containing the follicular fluid proteins will be transferred to a fresh tube. Further, protein estimation will be performed using BCA assay. Since quantitative proteomics needs to be performed through in-solution trypsin digestion, the high abundant proteins present in the follicular fluid will be enriched using Proteominer enrichment kit from Bio Rad. The enriched protein fractions will be eluted, and further protein estimation was done using BCA assay. These protein samples will be resolved on a 15% SDS-PAGE gel to see the overall protein profile after protein enrichment.

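### The follicular fluid is spun to remove cell debris and frozen before the step that should isolate its granulosa cells, and the three handling sections do not agree on the order

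*Protocol article*

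**What the plan says.** The protocol article describes the handling of follicular fluid in three places.

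- **Data collection, follicular fluid paragraph.** The fluid, "after removing the cell debris through centrifugation" at 700 g for 10 min, goes at once into liquid nitrogen, is carried to the School of Biotechnology, divided into aliquots there and kept at −80 °C. The paragraph mentions no Percoll, no cell fraction and no cryoprotectant.
- **Transcriptomics of granulosa cells.** "Granulosa cells will be isolated from the follicular fluid by centrifugation at 700 g for 10 min using percoll-mediated density gradient centrifugation". The cell layer is then "transferred to a fresh tube with the cell storage medium", which is 10% FBS with DMSO, and RNA is extracted from the cells.
- **Proteomics of follicular fluid.** "The follicular fluid collected will be subjected to percoll-mediated density gradient centrifugation", again at 700 g for 10 min, and "the supernatant containing the follicular fluid proteins will be transferred to a fresh tube".

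The metabolomics section goes directly to solvent extraction of the sample and names no Percoll. Trial settings places the multi-omics analysis after transfer to the School of Biotechnology. Under Objectives, granulosa-cell transcriptomics is the first exploratory secondary objective.

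**The concern.** The clinic step and the cell-isolation step use the same force and duration but serve opposite purposes. One clears cellular material out of the fluid before freezing. The other is meant to collect the cells from that fluid. If staff carry out the sections in the order in which the sample travels, the cells needed for RNA sequencing may be gone, or may already have been frozen without protection, when the isolation step is reached.

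At stake are the first secondary objective and the transcriptomic layer of the planned integration (MOFA, with correlation to AMH and AFC changes). The loss would be hard to repair, because Table 1 schedules follicular fluid collection at one visit only, oocyte pick-up. The RNA check named in the article (purity and concentration by Nanodrop) comes after the material has been collected and frozen, so it could reveal a low yield but not restore it.

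**Working it through.** The article gives no figure to reproduce here. The check sets the steps side by side.

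| Section | Force and time | Percoll | Fraction the text follows | What happens next |
|---|---|---|---|---|
| Data collection | 700 g, 10 min | not mentioned | fluid | liquid nitrogen at once, transport, aliquots, −80 °C |
| Transcriptomics | 700 g, 10 min | yes | cell layer | FBS/DMSO medium, then RNA extraction |
| Proteomics | 700 g, 10 min | yes | supernatant | protein assay and enrichment |
| Metabolomics | no spin before extraction | not mentioned | fluid | solvent extraction |

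Three readings are possible.

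1. **Clinic spin first, cells come down with the debris.** The transcriptomics and proteomics sections rely on this force and time to part cells from fluid. It is an assumption, though a natural one, that a plain spin at the same setting takes most cells down too. The Percoll step would then start from cell-depleted fluid. No section says that the removed fraction is kept.
2. **Clinic spin first, cells stay in the fluid.** The cells enter liquid nitrogen before they meet the DMSO medium. Aliquoting follows transport in liquid nitrogen and precedes storage at −80 °C, which implies a thaw and a second freeze before any isolation in the laboratory. A DMSO storage medium has a clear purpose only if cells are separated before they are frozen.
3. **The clinic spin is itself the Percoll step, with the cell layer saved at the clinic.** This would work. But Data collection names no Percoll, calls the removed material debris, sends the fluid to liquid nitrogen immediately and mentions no cell tube. The reading is possible but has to be supplied by the reader.

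Readings 1 and 2 are alternatives, so their harms do not add up.

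Size: 10 treated + 10 control = 20 women give fluid, so at most 20 of 20 RNA samples are exposed. Transcriptomics is one of three layers (transcriptomics, proteomics, metabolomics), so 1 of 3 is at risk in the integration.

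**The case against.** The strongest reply is that this is a condensed article and that bench order belongs in a standard operating procedure. The article says that such procedures will be followed at every level of data handling, and the transcriptomics workflow figure is not available in the text reviewed. The transcriptomics section also moves from aspiration and pooling at retrieval directly to cell isolation and a DMSO medium, which suggests separation of fresh cells. Data collection could then be a shortened account of the fluid fraction alone.

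Much of this stands. A reader might infer that the two spins are one and the same, that the cells are thrown away, or that the objective has no usable material. The documents do not support any of these as fact: force and time match, but only the transcriptomics and proteomics sections name Percoll; no sentence says that the removed fraction is discarded; and harvest at the clinic is not excluded.

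A reader might also infer that cell contents leak into the proteomic and metabolomic samples in amounts that track ovarian reserve. Nothing in the article bears this out. It could arise only under the second reading, and the controls are to be matched on age and baseline AMH/AFC.

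What the reply does not remove is the conflict in what is printed. The article gives force, minutes, container, tube size and storage temperature. At that level of detail, a procedure that saves the cells would have to add to or depart from the Data collection paragraph.

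**Conclusion.** The concern holds as a conflict between stated procedures, not as a demonstrated loss. Followed in the written order, the sections leave the granulosa cells either removed without stated retention or frozen without cryoprotectant. The exposure is up to 20 of 20 RNA samples and one of three omics layers, with one planned collection per woman.

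This rests on two assumptions: that the Data collection steps come before the transcriptomics steps, as the transfer in Trial settings suggests, and that no unseen procedure overrides them. If cells are in fact harvested at the clinic, the defect is only one of wording.

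The multi-omics work is exploratory and hypothesis-generating, with no formal sample size. The AMH and AFC outcomes, the 30 treated participants and their paired analysis are untouched. The point therefore deserves correction before further retrievals but does not threaten the trial's main result.

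**What to change.** State one sequence, identical for all 20 women so that handling cannot differ between treated and control samples:

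1. At the fertility centre, recover the granulosa cells from fresh fluid before any freezing. Keep the cell fraction of the clinic spin, take it to Percoll isolation, and place the cells in storage medium or RNA reagent.
2. Then freeze the cell-depleted fluid for proteomics and metabolomics.

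Align Data collection and the transcriptomics, proteomics and metabolomics sections with this order. Say where the Percoll step takes place and whether the proteomics section still needs its own. Keep the metabolomics aliquot free of Percoll, because that section specifies none; sending it Percoll-processed supernatant would change the sample material unless the section is amended to say so.

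The cost is a revision of the protocol and operating procedure, plus Percoll, storage medium or RNA reagent, tubes and some bench time at a centre that already runs a 700 g, 10 min spin. If the existing procedure already works this way, only the wording has to change.
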